### Ethical approval

This trial has received ethical approval through the Tasmanian Health and Medical Human Research and Ethics Committee. Approval number: H11821. All participating patients will provide informed consent.

## Discussion

Recent evidence supports the current need for an intervention directed at improving the prescription of, and patients' adherence to, guideline-based therapy in the period following ACS hospital discharge [2,3]. This trial aims to achieve this outcome using an intervention that is based on only minor adjustments to a currently existing and funded service, such that any success derived from this trial may be easily translated into regular practice. The potential for providing directly applicable benefits to society by using this proposed method was recognized in a recent editorial by Davidson and Macdonald [67]. Should our intervention lead to an improvement in the primary outcome, the inherent sustainability of the intervention in a real world environment is one of its major strengths.

As mentioned through this paper, the DMACS study demonstrated significant improvements in prescribing at discharge, but these improvements were almost completely lost at three months post-discharge [3]. Therefore it could be proposed that, ideally, the intervention described within this trial would occur in conjunction with a similar quality improvement study. This would ensure that both the in-hospital and post-discharge aspects of management were addressed together, allowing for an even greater opportunity to demonstrate sustained improvements. As the specific benefits from a dHMR service directed at ACS patients are unknown, however, it is logical to trial this service first, before considering its position in conjunction with other interventions. Australia's National Prescribing Service offers kits to allow ongoing drug use evaluations similar to that of the DMACS study, therefore a trial combining an in-hospital intervention and a post-discharge dHMR may be feasible for future research, should the current trial lead to success worthy of this follow-up.

Although based on an existing, Medicare-funded service, the treatment protocol faces several potential barriers to success. Largely, this includes interprofessional barriers, such as GP approval of the dHMR referrals and GP acceptance of pharmacists' recommendations. The former point will be aided by the enrolling researcher contacting the GP once randomization has been revealed. Although GP approval of dHMR referrals may affect the uptake of the intervention in this trial, the use of a consistent and informative referral letter and a telephone conversation to support this letter, could prove to be advantageous over the current systems for initiating standard HMR referrals, which may not always be this well-structured. The other barrier of GPs not accepting pharmacists' recommendations has been raised due to previous research showing that GPs only action approximately 45% of pharmacist's recommendations following HMRs [68,69]. The educational material provided to accredited pharmacists completing this trial, however, should help guide pharmacists to make recommendations which will be relevant post-ACS and simple to implement. Furthermore, as the education package has been based on the latest evidence in ACS management, even if GPs do not accept all of the pharmacists' recommendations, they should still be gaining useful information from the dHMR reports. This may lead to improved ACS management, irrespective of the rate at which GPs accept pharmacists' individual recommendations.

Having the pharmacists complete the online training package may also be another barrier to the successful implementation of the trial protocol. The education and assessment package should take approximately three hours to complete and will be rewarded with recognition of continuing professional development and an AUD$50 honorarium. We hope that these incentives and the easy-to-use format of the material will help facilitate the completion of the package. Through careful consideration of the potential barriers recognized above, the dHMR processes that we have developed have transformed these barriers into opportunities to improve the implementation of the intervention.

We have designed a trial to test the effect of minor changes to an existing, funded model of intervention to target the needs of a high-risk population. The conceptually derived intervention, based on the Lemmens *et al. *framework, accommodates funding and other health-system-related barriers which are critical for successful implementation. The intervention will be assessed by observing changes in medication adherence which is an outcome that appropriately matches the aim of the intervention. We have outlined the potential benefit from the application of this intervention on a worldwide scale, should the intervention demonstrate positive outcomes in the trial population of Australian ACS patients.

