## Abstract

**Background:**

Despite continual improvements in the management of acute coronary syndromes, adherence to guideline-based medications remains suboptimal. We aim to improve adherence with guideline-based therapy following acute coronary syndrome using an existing service that is provided by specifically trained pharmacists, called a Home Medicines Review. We have made two minor adjustments to target the focus of the existing service including an acute coronary syndrome specific referral letter and a training package for the pharmacists providing the service.

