## Methods/Design

### Overview

We will conduct a randomized controlled trial comparing the dHMR service delivered at two months post-discharge to usual care following an ACS admission. Changes in the pharmacist referral process and an ACS-specific education package to be completed by the study pharmacists make this program different to the standard HMR service. The primary outcome will be the proportion of patients who are adherent to a complete, guideline-based ACS medication regimen at six and twelve months post-discharge. Patients will be enrolled in hospital during an admission for ACS. Figure 1 provides an overview of the trial protocol. The design of the intervention and monitoring system has been based on a conceptual framework for the standardized evaluation of chronic disease management interventions, as developed by Lemmens *et al. *[28]. Figure 2 is a summary of this framework and Figure 3 is a comparison of how the components of this trial compare against the Lemmens *et al. *framework.

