### Randomization

We will use a computer-generated random sequence to provide the randomization coding. Patients will be randomized to the control or intervention groups following computerized recognition that the patient meets the inclusion criteria and has consented to trial involvement. The correct entry of this information into the central trial database will then enable the enrolling researcher to unlock the randomization status for that participant.

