### Intervention

Patients in the intervention group will receive a dHMR at approximately two months following discharge as well as usual care. The time of two months post-discharge was selected as previous studies of ACS patients have demonstrated that the period between one and three months post discharge is when patients are most vulnerable for medication discontinuation [2,3,32]. This suggests that a service addressing both the educational and clinical management aspects of therapy may be most beneficial when offered in this time period.

Based on the existing funding arrangements and recommended reasons for referral, the HMR service is currently available in Australia for all ACS patients following hospital discharge [16]. The uptake of this service, however, may be largely limited by the absence of HMR referral systems in this transitional period. Furthermore, the currently available service could be tailored to maximize the potential for benefit from this service in the ACS population. We propose to add to the existing HMR service in several ways, making the proposed dHMR service more directed toward the ACS population.

Typically, HMRs are ordered by a referral letter generated by the patient's GP. Referral letters may vary significantly in their level of detail, potentially leaving the pharmacist with little direction prior to the patient interview. This concern was highlighted as a potential downfall of the service in a qualitative review that was conducted in 2008 [15]. To address this issue, the enrolling researchers will use a specifically designed database that allows baseline data collection to automatically populate sections of the HMR referral. The referral letter will still be sent to the GP for approval and addition of any further information, such as medications that have changed since discharge. GP approval is a requirement for payment under the existing public service arrangements, and having the GP engaged with the intervention early should increase their willingness to participate. This new approach, however, relieves the GP from having to complete most of the referral data and allows for simple addition of only useful information. The GP may also find the information on this referral letter useful when they receive the letter, as previous research has demonstrated that standard discharge letters following ACS admissions do not always contain a sufficient level of information and sometimes take too long to reach the GP [3].

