### Secondary outcomes

Secondary outcomes will include hospital readmission rates, length of hospital stays, changes in quality of life, cardiac rehabilitation completion rates, smoking cessations rates, and mortality. Hospital readmissions and mortality will be further categorized as ACS-related or due to other causes. Quality of life will be measured at six weeks post-discharge as a baseline, pre-dHMR measure and again at both study endpoints. The Euroqol 'EQ-5D 3 L' [42] will be used to measure general quality of life and the Seattle Angina Questionnaire (SAQ) [43] will be used to measure cardiac-specific quality of life. Both instruments have been validated when administered individually [43-46] and in combination [47] to assess quality of life in patients with coronary heart disease. In addition to a self-report of smoking status at baseline and the study endpoints, we will be further categorizing each smoker's dependence on cigarette smoking using the Fagerstrom Test for Nicotine Dependence (FTND) [48].

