### Statistical analysis

All baseline variables will be compared between the control and intervention groups using independent samples t-tests for continuous variables and chi-squared analysis for categorical variables. All outcomes will be reported as descriptive comparisons between the control and intervention groups, with significance reported at alpha = 0.05. Where primary outcomes reach statistical significance, any noted difference in the baseline group comparison will be tested by univariate comparison with stepwise addition into a multivariate model for those with univariate significance of *P *< 0.1. Changes in each group's questionnaire results between baseline and study endpoints, as well as differences between intervention and control group's questionnaire results, will be reported. Further correlational investigations between questionnaire results and adherence will be reported elsewhere. As there are several potential barriers that may prevent a patient randomized to the intervention group from receiving a dHMR according to the protocol, we will use both an intention-to-treat analysis as well as an on-treatment sensitivity analysis.

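### The six-week questionnaires are called baseline but follow randomisation and probably intervention-arm GP contact, so change scores and stepwise adjustment could remove any early effect of allocation

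*Protocol article*

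**What the plan says.** The order of events has to be put together from several sections of the protocol article.

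- **Enrolment** (Overview): "Patients will be enrolled in hospital during an admission for ACS".
- **Allocation** (Randomization): "Patients will be randomized to the control or intervention groups following computerized recognition that the patient meets the inclusion criteria and has consented".
- **What defines the intervention** (Abstract, Background): "two minor adjustments to target the focus of the existing service including an acute coronary syndrome specific referral letter", the other adjustment being the pharmacist training package.
- **GP contact** (Discussion): the text names GP approval of the referral as a barrier and then says "The former point will be aided by the enrolling researcher contacting the GP once randomization has been revealed". It goes on to describe "the use of a consistent and informative referral letter and a telephone conversation to support this letter".
- **Possible value of the letter in itself** (Intervention): "The GP may also find the information on this referral letter useful when they receive the letter". The reason given is that ordinary discharge letters can be thin and slow to arrive. The same section wants the GP involved early.
- **The visit** (Intervention): about two months after discharge.
- **The label** (Secondary outcomes): "Quality of life will be measured at six weeks post-discharge as a baseline, pre-dHMR measure and again at both study endpoints". Data collection likewise lists the six-week questionnaire set as the last baseline collection point.
- **The use made of it** (Statistical analysis): "Changes in each group's questionnaire results between baseline and study endpoints" will be reported, along with differences between the two groups. All baseline variables are compared between arms. If a primary outcome is significant, noted baseline differences are tested for stepwise entry into a multivariate model at P < 0.1.

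**The concern.** A baseline should be measured before allocation can influence it. The six-week questionnaires come after randomisation, and two routes could let allocation affect them.

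The first is the GP. The researcher's call and the structured letter belong to the intervention referral, so control GPs have no reason to receive either.

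The second is the patient. Under Data collection, intervention patients are asked to complete the form before the pharmacist comes, so they answer questions on adherence, beliefs and self-efficacy knowing that a visit is due.

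Two analyses are exposed:

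- Change scores subtract the six-week value and, with it, any difference that allocation has already produced.
- The compare-then-adjust rule treats a between-arm difference in a baseline variable as chance imbalance. A six-week adherence or belief score could be something allocation changed on the way to better adherence. Entering it in the model for the primary outcome would then adjust away part of the effect under test.

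**Working it through.** **Plan's own figure.** The protocol gives no number for an early effect. Its one design calculation, the sample size, reproduces: 45% against 60%, two-sided alpha 0.05, 80% power and a continuity correction give 186 per group, and 372 / 0.8 = 465. It does not enter this point.

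**Step 1: is the six-week score post-randomisation?** Yes. Enrolment is in hospital, allocation is unlocked once eligibility and consent are entered, and the questionnaire is mailed six weeks after discharge.

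**Step 2: has the GP contact happened by then?** Probably, but no date is given.

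- For: contact follows the reveal of allocation; the GP is to be involved early; the letter is filled from data collected at enrolment; and its claimed advantage over slow discharge letters makes sense only if it arrives promptly.
- Against: the GP is asked to add medication changes made after discharge, so the letter may be handled somewhat later. Two months is about 8.7 weeks, which leaves 8.7 − 6 = 2.7 weeks after week six in which approval could still be obtained.

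**Step 3: effect on the estimates.** Let D be the between-arm difference at an endpoint, e the difference caused by allocation by week six, and b the slope of the endpoint score on the six-week score.

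- Endpoint comparison: D
- Difference in change scores: D − e
- Analysis adjusted for the six-week score: D − b·e

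The documents give neither e nor b. The table shows the share of D retained for assumed values, with e in the same direction as D.

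| e/D | Endpoint | Change score | Adjusted, b = 0.3 | b = 0.5 | b = 0.7 |
|---|---|---|---|---|---|
| 0% | 100% | 100% | 100% | 100% | 100% |
| 10% | 100% | 90% | 97% | 95% | 93% |
| 20% | 100% | 80% | 94% | 90% | 86% |
| 40% | 100% | 60% | 88% | 80% | 72% |

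**Step 4: reach into the primary outcome.** The medication possession ratio comes from dispensing records and subtracts nothing measured at week six, so the unadjusted comparison is safe. The adjusted comparison is not protected. Data collection counts the six-week set as baseline, and Statistical analysis puts every baseline variable through the comparison and, where a difference is noted, through stepwise selection.

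**Step 5: price in precision.** Assume equal variances at both times and correlation r between the six-week and endpoint scores. Relative to the endpoint comparison (variance 1), change scores have variance 2(1 − r) and adjusted analyses 1 − r². At r = 0.5 these are 1.00 and 0.75; at r = 0.7 they are 0.60 and 0.51.

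**The case against.** The case on the other side has real weight.

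- **Timing.** A reader might infer that treatment has definitely begun before week six. The documents do not establish that: neither letter nor call is dated, and the trial overview figure, which might show the timing, is not available here. For the pharmacist visit itself, the pre-dHMR label is accurate.
- **Mechanism.** The letter is designed mainly to direct the pharmacist, and the call to secure approval. Usefulness to the GP is mentioned only as a possibility, and no route from GP contact to six-week questionnaire scores is described. An early effect near zero is credible.
- **Size.** A reader might take 10% to 40% as the expected loss. It is an assumption, and nothing is lost if e is zero.
- **Existing safeguard.** Outcomes says that each outcome is compared between arms at six and twelve months, and Statistical analysis plans between-group questionnaire differences as well as changes. The protocol does not say which of the two carries the inference.
- **Reason for week six.** Data collection explains that in-hospital answers, for instance on adherence, may be unrepresentatively high. That is a fair reason to measure just before the visit.
- **Precision.** Barring the six-week score from every analysis would be a debatable trade. At assumed correlations of 0.5 to 0.7, it gives up a 25% to 49% variance reduction.

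These arguments limit the point and rule out discarding the six-week score. They do not make it a pre-randomisation value, and they do not answer the stepwise-adjustment problem.

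**Conclusion.** The concern holds in limited form. It is certain that the six-week questionnaire is a post-randomisation measurement labelled baseline. It is a strong inference, not a stated fact, that intervention-arm GP contact usually comes first. Any difference allocation has produced by then is removed in full from change scores and in part from analyses adjusted for the six-week score. The size is unknown and may be zero. For these questionnaire variables, a between-arm comparison at six weeks is not a clean check on randomisation, and the stepwise rule could carry an affected score into the adjusted primary analysis.

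A reader might go further and conclude that the main trial result is biased. The documents do not support that: the unadjusted possession-ratio comparison, readmissions, length of stay and mortality do not use the six-week score, and the planned between-arm questionnaire comparison recovers D whatever e is. The point is still worth correcting, because Trial status says recruitment has not started and the remedy is wording.

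**What to change.** 1. In Secondary outcomes, Data collection and Statistical analysis, describe the six-week questionnaire as a post-randomisation, pre-visit measurement. State when the letter and call are made relative to it.
2. In Statistical analysis, let the between-arm comparison at six and twelve months, already planned there and in Outcomes, carry the inference for questionnaire outcomes.
3. Keep change from week six, or adjustment for the six-week score, as a supportive analysis of the period starting just before the visit.
4. Restrict the baseline comparison and the covariate adjustment of the primary outcome to variables recorded before allocation is unlocked.

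No new data are needed. The cost is some precision in the lead analysis of the questionnaire outcomes only: none against change scores at an assumed correlation of 0.5, more at higher correlations or against an adjusted analysis. Keeping those analyses as supportive retains most of what they offer.

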## Trial status

The trial has not yet started recruiting. The expected start time is early 2012.

## Abbreviations

ACE inhibitor: Angiotensin-Converting Enzyme Inhibitors; ACS: Acute Coronary Syndromes; AP: Accredited Pharmacist; ARBs: Angiotensin II Receptor Blockers; BMQ: Beliefs About Medicines Questionnaire; Brief IPQ: Brief Illness Perception Questionnaire; CABG: Coronary Artery Bypass Graft; CCU: Coronary Care Unit; CR: Cardiac Rehabilitation; dHMR: Directed Home Medicines Review; DMACS: Discharge Management of Acute Coronary Syndrome; FTND: Fagerstrom Test for Nicotine Dependence; GP: General Practitioner; HMR: Home Medicines Review; IHMRS: INTERHEART Modifiable Risk Score; LGH: Launceston General Hospital; MPR: Medication Possession Ratio; PCI: Percutaneous Coronary Intervention; PHRQ: Perceived Health Risk Questionnaire; QOL: Quality Of Life; RHH: Royal Hobart Hospital; SAQ: Seattle Angina Questionnaire; TABS: Tool for Adherence Behavior Screening
